### Sample size

The MAINTAIN feasibility RCT will assess recruitment rate, adherence, acceptability, and clinical, physiological, and health-related outcomes. The study also aims to identify a primary outcome and estimate a sample size to inform a future definitive RCT based on long-term exercise adherence and health outcomes between the two treatment arms.^48^ However, assuming a medium effect size (0.5) for a repeated measures ANOVA, between two groups over four timepoints with an alpha of 5% and a beta of 90%, a total of 30 participants would be required.^49,50^ Due to the novelty of the proposed outcome measures, a medium effect size will be applied.^51^

From local data (UHCW NHS Trust), 255 patients per year have been identified as accessing community CR of which 212 have a diagnosis of coronary heart disease (CHD). Over a 24-month recruitment period, this provides a potential pool of 510 patients. Local audit data suggests at least 83% of these patients are eligible. Therefore, of these 510 local patients, 423 are potentially eligible, of which we aim to recruit 30 (i.e., approximately 7%, at an approximate rate of five per month).

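### Thirty participants do not give 90% power for a medium (0.5 SD) difference between arms; the figure of 30 arises only for a large effect, and the effect-size scale is not named

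*Protocol article*

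**What the plan says.** The Sample size section first lists the feasibility aims and the aim of informing the size of a later definitive trial. It then gives a power calculation: "assuming a medium effect size (0.5) for a repeated measures ANOVA, between two groups over four timepoints", and finally "a beta of 90%, a total of 30 participants would be required". The choice of effect is explained by "Due to the novelty of the proposed outcome measures, a medium effect size will be applied".

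The section does not say whether 0.5 is d or f, which ANOVA effect is powered (group main effect or group-by-time interaction), or what correlation between visits was assumed. The abstract and the Objectives give 30 as the number to be randomised, 15 per arm. The Data analysis section plans a mixed model ANOVA of follow-up differences and of changes from baseline. It sets alpha at 0.05 and provides for post hoc tests after significant results, yet also says that there will be no formal hypothesis testing.

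**The concern.** The word medium and the number 0.5 belong together on the d scale, where 0.5 is half a standard deviation between arms. A repeated measures ANOVA calculation takes f as its input. On that scale medium is 0.25, and with two groups f = d/2, so f = 0.5 is a difference of one full SD. A reader who meets a medium effect of 0.5 will take the trial to have 90% power for half an SD. Fifteen per arm looks far too few for that.

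What is at stake is interpretation. The trial is meant to help choose a primary outcome and estimate the size of a definitive trial. If arm differences are judged against a power figure that the design does not have, an outcome with a moderate true effect could be set aside because it showed no significant difference.

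Two smaller points sit in the same sentence. Beta is the type II error rate, so power is meant. And the calculated requirement equals the number randomised, so no loss over 12 months is allowed for, although withdrawal and retention are among the primary outcomes.

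**Working it through.** **Inputs from the protocol article.** Two groups, 1:1; m = 4 timepoints; alpha 0.05; power 0.90 (printed as beta); effect size 0.5, called medium; N = 30.

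**Assumptions, not in the document.** Equal correlation ρ between all visits, taken as 0.5 and varied from 0.3 to 0.8; sphericity; complete data unless stated.

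**Formulas (noncentral F).**
- Group main effect: λ = N f² m / (1 + (m − 1)ρ), df 1 and N − 2.
- Group-by-time interaction: λ = N f² m / (1 − ρ), df 3 and 3(N − 2).

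**Step 1: reproduce 30 at ρ = 0.5.**

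| Effect tested | f | λ at N = 30 | Power at N = 30 | Smallest even N for 90% |
|---|---|---|---|---|
| Group main effect | 0.5 | 30 × 0.25 × 4 / 2.5 = 12.0 | 0.917 | 30 |
| Interaction | 0.25 | 30 × 0.0625 × 4 / 0.5 = 15.0 | 0.903 | 30 |
| Group main effect | 0.25 | 30 × 0.0625 × 4 / 2.5 = 3.0 | 0.387 | 108 |
| Interaction | 0.5 | 30 × 0.25 × 4 / 0.5 = 60.0 | above 0.99 | 10 |

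The first two rows match the stated 30. (The time main effect with f = 0.25 gives the same numbers as the second row, but it does not compare arms.) Both matches depend on ρ. Over ρ = 0.3 to 0.8, the first row's N runs from 24 to 38 and the second row's from 42 to 14.

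**Step 2: translate the two matches into SD units.**
- Main effect, f = 0.5: d = 2f = 1.0 if the difference is present at all four visits. Randomisation makes the expected baseline difference zero. With differences (0, d, d, d) the average is 0.75d, so f = 0.375d and d = 0.5/0.375 = 1.33 at follow-up.
- Interaction, f = 0.25: with differences (0, d, d, d), each arm deviates by half the difference. The root mean square of the centred half-differences is 0.2165d, so d = 0.25/0.2165 = 1.15 at every follow-up.

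**Step 3: power at N = 30 if the true difference is 0.5 SD at all three follow-ups.** For the interaction, f = 0.2165 × 0.5 = 0.108, so at ρ = 0.5 λ = 30 × 0.01172 × 4 / 0.5 = 2.81. The baseline-adjusted mean of three follow-ups has residual SD √((1 + 2ρ)/3 − ρ²), which is 0.645 at ρ = 0.5. Its noncentrality is (0.5/0.645) × √(15/2) = 2.12 on 27 df. The single-visit t-test has noncentrality 0.5 × √(15/2) = 1.37 on 28 df and does not involve ρ.

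| Analysis | ρ = 0.3 | 0.5 | 0.7 | 0.8 |
|---|---|---|---|---|
| Interaction test | 19% | 25% | 40% | 57% |
| Group main effect (baseline difference zero) | 30% | 24% | 20% | 19% |
| Single-visit t-test | 26% | 26% | 26% | 26% |
| Baseline-adjusted mean of three follow-ups | 51% | 53% | 66% | 79% |
| Difference detectable with 90% power, interaction test | 1.36 SD | 1.15 SD | 0.89 SD | 0.73 SD |

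The interaction test reaches 90% at 0.5 SD only when ρ is about 0.905.

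**Step 4: loss to follow-up.** With 24 completers (an illustrative 20% loss) and ρ = 0.5, the main-effect route has λ = 9.6 and power 84%; the interaction route has λ = 12.0 and power 82%.

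**The case against.** The strongest reply is that nothing was miscalculated. An effect size of 0.5 entered as f in a repeated measures ANOVA does return 30, and so does f = 0.25 on the interaction. That stands: a reader might infer an arithmetic error, and the documents do not support it.

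Second, the article never says that 0.5 is a follow-up difference in SD units. A reader might infer that power is simply 25%, or that only differences above 1 SD can be detected. Both figures need an assumed correlation and a constant effect across follow-ups. At a correlation of 0.7 the interaction test already detects 0.89 SD, and a baseline-adjusted analysis does considerably better than the ANOVA tests. These figures have to be given as ranges. What survives is that no analysis tried reaches 90% at 0.5 SD for correlations of 0.3 to 0.8.

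Third, an article may leave the correlation and the tested effect to the full protocol. That is fair, and their absence alone would not be a finding. But the claim that the article does print, 90% power for a medium effect of 0.5, is not met by either route to 30, so the missing detail cannot rescue it.

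Fourth, this is a feasibility trial that disclaims formal testing. This limits the consequence, since the primary outcomes do not rest on the power figure. It does not remove it, because the Data analysis section still sets a significance level and lets significant results trigger further tests.

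Finally, reading the beta slip as 10% power would be pedantic. It is plainly meant as power.

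**Conclusion.** The concern holds as a mislabelled and underspecified effect size. The number 30 is consistent with 90% power only for a large between-arm effect: d = 1.0 on the group main effect, or about 1.15 SD at every follow-up on the interaction, each at an assumed correlation of 0.5. It is not consistent with 90% power for a medium difference of 0.5 SD. The direction of the shortfall is secure over the correlations examined; its exact size is not, because the article does not fix the correlation or the effect profile.

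Importance is moderate. A reader might infer that the trial is too small and should be enlarged. The documents do not support that: the primary outcome is feasibility, and 30 can be defended on that ground. Nor is it established that a null result will be misread; the printed claim merely invites it.

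**What to change.** Keep 30 and remove the statement of 90% power for a medium effect. Justify the number by the precision it gives:

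- For retention, as an illustration, 24 of 30 retained (80%) has an exact 95% confidence interval of 61% to 92%. The 24 is an example, not a rate taken from the article.
- For an unadjusted between-arm difference with 15 per arm, the 95% confidence interval half-width is 2.048 × √(2/15), about 0.75 SD.

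If a power figure is kept, write power in place of beta. State the scale (d or f), the ANOVA effect, the assumed correlation and the allowance for dropout. Describe the effect that 30 detects as large, and show it over a range of correlations rather than at one assumed value.

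The cost is wording only: no extra participants, and no change to outcomes or analysis. The stated figure becomes less favourable.

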**Figure 1. fig1-20552076231152176:**
[figure not shown]
Schedule of enrolment, interventions, and assessments.

**Table 1. table1-20552076231152176:** World health organization trial data set.

Data category	Information
Primary registry and trial identifying number	NCT05292287
Date of registration in primary registry	22/03/2022
Secondary identifying numbers	REC reference: 21/LO/0705 IRAS Number: 302243 Protocol number: P121990
Primary sponsor	Coventry University [name] [contact]
Secondary sponsor	N/A
Contact for public queries	Email: [contact]
Contact for scientific queries	[name] Centre for Sport, Exercise and Life Sciences Research Institute for Health & Wellbeing Coventry University [name] Email: [contact]
Public title	Long-term CR using remote exercise prescription and monitoring via a wearable device
Scientific title	reMote mAINTenance cArdiac rehabIlitatioN (MAINTAIN): a randomised controlled feasibility study
Countries of recruitment	England
Health condition(s) or problem(s) studied	Coronary heart disease
Intervention(s)	Intervention group: initial exercise consultation; personalised exercise prescription delivered via a Polar Ignite watch; monitoring via check-ins and feedback text-message support. Control group: usual care
Key inclusion and exclusion criteria	Inclusion: Coronary heart disease; Completed a community centre-based CR programme; clinically stable (symptoms and medication), access to a smartphone with Bluetooth capacity or a computer/laptop/tablet; able to walk unaided; able to provide informed consent. Exclusion: Absolute contra-indications to exercise as per international clinical guidelines ^31^; Any serious mental health/cognitive issue that will prevent engagement with study procedures or increase the risk of exercise complications; atrial fibrillation or other arrhythmia preventing accurate heart rate monitoring; allergies to the watch materials
Study type	Type: feasibility, interventional, single centre Allocation: randomised Assignment: parallel Masking: outcomes assessor
Date of first enrolment	TBC
Target sample size	30
Recruitment status	Ready to start recruitment

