### Participant identification, recruitment, and informed consent

Potential participants will be identified from existing supervised or home-based CR attendees at UHCW NHS Trust by the clinical team on site (Figure 1). Screening logs will be completed when assessing eligibility, and reason(s) for non-participation will be recorded beginning on the 30^th^ of March 2022 until 30 participants are randomised. Potential participants will be approached by the clinical team either in person, or via phone call, email, or post. Those who are interested will be given information about the study verbally and in a printed participant information leaflet. Once willingness to participate has been confirmed, the participant will be asked to attend a baseline assessment to confirm eligibility and complete written informed consent.

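### The recruitment projection does not fit together: 30 participants over 24 months is 1.25 per month, not five, and 423 eligible is practically every patient with CHD

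*Protocol article*

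**What the plan says.** The projection stands in the second paragraph of Sample size in the protocol article. It starts from local data: "255 patients per year have been identified as accessing community CR of which 212 have a diagnosis of coronary heart disease (CHD". It continues: "Over a 24-month recruitment period, this provides a potential pool of 510 patients". It then says: "Local audit data suggests at least 83% of these patients are eligible". From this it derives 423 potentially eligible patients, "of which we aim to recruit 30 (i.e., approximately 7%, at an approximate rate of five per month".

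Table 1 sets the entry criteria. Besides CHD, one of them is "Completed a community centre-based CR programme". Others concern clinical stability, access to a suitable device, walking without aid, contra-indications to exercise, mental health or cognition, and arrhythmia that would spoil heart-rate recording. The section on participant identification describes the source population more widely: "Potential participants will be identified from existing supervised or home-based CR attendees". It lets screening run from 30 March 2022 until 30 people are randomised and gives no end date.

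Numbers screened, eligible and recruited are among the primary outcomes (Table 1 and Outcome measures), and Sample size lists recruitment rate among the things the trial will assess.

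**The concern.** Three things do not fit.

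- **Rate against period.** The 7% rests on a 24-month pool, while the monthly rate implies a much shorter period.
- **The eligible share.** The 83% equals, to rounding, the share of attenders who have CHD. That raises the question whether the other entry criteria were applied.
- **Who is in the pool.** Table 1 refers to centre-based rehabilitation, while the identification section also draws on home-based attendees.

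This paragraph holds the only numerical recruitment expectation in the document. A site recruiting 1.25 per month would match the stated uptake and fall four-fold short of the stated rate, so a reader of the results could not tell whether recruitment went as expected. Anyone who took the figures forward to plan sites and duration for the definitive multi-centre trial would get very different answers from the two versions.

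**Working it through.** **Inputs** (all from Sample size): 255 attenders per year; 212 of them with CHD; 24 months; 83% eligible; target 30; about 7%; about five per month.

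**The plan's own figures**

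- Pool: 2 × 255 = 510. Reproduced.
- Eligible: 0.83 × 510 = 423.3. Reproduced as 423.
- Uptake: 30/423 = 7.1%. Reproduced.
- Rate: 30/24 = 1.25 per month. The stated five per month is not reproduced; 5/1.25 = 4.

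**Which combinations are consistent**

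| Held fixed | Follows | Potentially eligible in that time | Uptake |
|---|---|---|---|
| 30 participants, 24 months | 1.25 per month | 423 | 30/423 = 7.1% |
| 30 participants, five per month | 30/5 = 6 months | 0.83 × 510/4 = 105.8 | 30/105.8 = 28.3% |
| Five per month, 24 months | 5 × 24 = 120 participants | 423 | 120/423 = 28.4% |

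Only the first two rows keep the target of 30.

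**The 83%**

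- CHD share: 212/255 = 83.1%. CHD patients in two years at the same annual number: 2 × 212 = 424.
- CHD is an entry criterion, so at most 83.1% of all attenders can be eligible. The plan says at least 83%.
- Taken together, 423 of about 424 CHD patients would have to meet every other criterion. Even if 83% was rounded up from 82.5%, the count is 0.825 × 510 = 420.8, so only about 3 of 424 would be excluded.
- If the 83% was meant to apply to CHD patients only, the eligible number is 0.83 × 424 = 352 and the 24-month uptake is 30/352 = 8.5%. The stated 423 would then be wrong.

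**Sensitivity to the other criteria.** The documents do not say what share of CHD patients meets them. For an assumed range of 100% down to 50%:

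- over 24 months, uptake among eligible patients is 30/424 = 7.1% up to 30/212 = 14.2%;
- over 6 months, it is 30/106 = 28.3% up to 30/53 = 56.6%.

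**The pool definition.** Table 1 asks for a completed centre-based programme. The identification section names supervised or home-based attendees. The aim, under Rationale for a randomised controlled trial, joins home-based and centre-based in one phrase that can be read either way. No figure shows how many of the 255 were home-based, so the effect on the count cannot be computed.

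**The case against.** The paragraph's purpose is to show that the local pool is large enough for 30 participants, and on either version it is. Screening runs until 30 are randomised, so neither the rate nor the 24 months stops recruitment. The trial will collect the real counts, and Data analysis summarises them descriptively, with the ADePT framework for appraisal. All of this stands and limits the severity. It does not make the stated figures agree, and a qualifier such as approximate does not cover a factor of four.

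A reader might infer more than the documents support:

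- **That the 7% is four-fold too low.** This holds only if five per month is intended. If 24 months is intended, 7% is right and the rate is wrong. The factor of four comes from rate against period alone; the 83% contributes nothing to it.
- **That the 83% is simply the CHD share relabelled.** The near-exact match suggests it, but the text credits local audit data, which cannot be seen. The match justifies asking for the source; it does not prove the origin.
- **That 7%, 83% or five per month are thresholds for going on to a definitive trial.** No section says so.
- **That home-based attendees would be screened and then turned away.** This is one reading. A home-based programme run from the centre might satisfy Table 1.

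**Conclusion.** The projection is internally inconsistent. Thirty participants in 24 months means 1.25 per month and 7.1% uptake; five per month means 6 months, about 106 potentially eligible patients and about 28% uptake. This rests only on figures in the paragraph and an even flow of patients over time.

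The eligible count is a separate weakness. If the second year resembles the first, 423 leaves practically no CHD patient excluded by any other criterion, and the text does not support that. Applied to CHD patients only, the 83% gives about 352 eligible and 8.5% uptake over 24 months. The wording on which rehabilitation completers qualify also needs reconciling, since it decides who is counted as eligible.

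The sample size of 30 does not come from this paragraph and is unaffected. No analysis or decision rule uses these figures. Severity: minor to moderate.

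**What to change.** 1. State one consistent set: either 24 months, 1.25 per month and about 7%, or 6 months, five per month and about 28%. The investigators know which was intended.
2. Give the source of the 83%, and say whether it applies to all attenders or only to those with CHD, and which entry criteria the audit checked. Unless it checked all of them, present 423 as the CHD pool, an upper bound on the number eligible. If it applies to CHD patients only, restate as about 352 eligible and 8.5% uptake over 24 months (or, over 6 months, 352/4 = 88 eligible and 30/88 = 34%).
3. Make Table 1, the aim and the identification section agree on whether home-based completers are eligible, so that the screening log counts one defined population.

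The cost is wording and one clarified criterion. No extra participants, data or analyses are needed.

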### Data analysis

Quantitative statistics will be summarised as mean and standard deviation (SD) or median and interquartile range (IQR) for normally and non-normally distributed continuous data, respectively, or frequency and percentage for categorical data at baseline, three-, six-, and 12-month post randomisation by treatment arms. Descriptive statistics will be presented by treatment arms. Data will be assessed for normality using the Shapiro-Wilks test to assess for heterogeneity between groups, baseline values will be compared using independent t-tests or Wilcoxon signed rank tests. Data regarding the number of participants expressing interest, eligible, consented, withdrawn, and lost to follow-up, as well as adherence to remotely prescribed exercise (for intervention arm) and outcomes assessments, will be summarised by treatment arms. Differences in mean outcomes between treatment arms at three-, six-, 12-month post-randomisation, and the difference of the change from baseline to three-, six-, 12-month post-randomisation between arms will be calculated and assessed using a mixed model ANOVA. Assuming the data meet the assumptions of an ANOVA, post hoc tests will be conducted on significant differences. Partial eta squared will be reported as effect sizes. All estimates will be reported with a 95% confidence interval. The alpha level will be set at 0.05. No formal hypothesis testing will be performed. Analysis and reporting of the MAINTAIN trial will be in line with the CONSORT statement.^52^ All primary analyses are planned to be on an intention-to-treat basis with a secondary per protocol analysis. The ADePT (A Process for Decision-making after Pilot and Feasibility Trials)^53^ framework will be used to identify and examine any problems which arise with the methodology. This appraisal of this study will help to find solutions to problems that arise and influence the process of progressing to a definitive RCT. All statistical analysis will be undertaken using IBM SPSS software.

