### Randomisation, allocation concealment, and blinding

Following completion of all baseline outcome measures, participants will be randomised to the intervention or control arm on a 1:1 ratio using a computer-validated randomisation system (Sealed Envelope Ltd, www.sealedenvelope.com) independent of the researchers to maintain allocation concealment according to the SPIRIT guidelines.^25^ The MAINTAIN intervention and semi-structured interviews will be completed by a researcher (FD) who will not be blinded to group allocation. All follow-up outcomes will be collected by research staff (AW) not involved in intervention delivery and will be blinded to group allocation. Participants will be asked not to inform the follow-up outcome assessor of their allocation.

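### The non-parametric test named for baseline comparisons is a paired test, but the two randomised arms are independent, and the baseline tests are not needed

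*Protocol article*

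**What the plan says.** The Data analysis section states that "baseline values will be compared using independent t-tests or Wilcoxon signed rank tests", depending on a Shapiro-Wilk check of normality. The stated purpose is "to assess for heterogeneity between groups".

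The Randomisation section says that "participants will be randomised to the intervention or control arm on a 1:1 ratio". Table 1 gives the assignment as parallel, and no matching or pairing of participants is described anywhere. On timing, the same section says: "Following completion of all baseline outcome measures, participants will be randomised".

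The Data analysis section also plans descriptive summaries by arm at baseline (mean and SD, or median and IQR). It sets a significance level ("The alpha level will be set at 0.05") and then says that "No formal hypothesis testing will be performed".

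**The concern.** Two things are wrong with the sentence on baseline comparisons.

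First, the two tests it names do not belong together. The independent t-test compares two separate groups. The signed rank test works on differences within pairs (or on one sample against a fixed value). Its counterpart for two separate groups is the rank-sum test. An analyst who follows the text for a non-normal variable would have to pair each intervention participant with an unrelated control participant, and the answer would depend on that arbitrary choice.

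Second, a p-value does not answer the question asked. Allocation follows baseline measurement and is random, so differences between the arms at baseline arise by chance. Whether a chance imbalance matters depends on its size and on how strongly the variable predicts outcome, and a significance test measures neither.

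At stake is the baseline table of a 30-person trial. It could carry p-values that cannot be reproduced, and readers could take the result of a test as evidence that the arms are, or are not, comparable.

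**Working it through.** **Inputs.** From the article: total 30, randomised 1:1, so 30/2 = 15 per arm; alpha 0.05; parallel assignment; baseline before randomisation. Assumed here, because the article does not give them: correlation 0.5 between repeated measures (step 1) and log-normal data for the illustrations (steps 3 and 5).

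**1. The plan's own figure.** The Sample size section says that "a total of 30 participants would be required". Take its effect size of 0.5 as Cohen's f for the between-group effect, with m = 4 timepoints, its 'beta of 90%' as 90% power, and correlation r = 0.5. The noncentrality is f² × N × m / (1 + (m − 1) × r).
- N = 30: 0.25 × 30 × 4 / 2.5 = 12.0, power 0.917.
- N = 28: 0.25 × 28 × 4 / 2.5 = 11.2, power 0.896.

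So 30 is the smallest even total that reaches 90%. The same total also follows from f = 0.25 for the within or interaction effect (power 0.903). No baseline test enters either calculation, so the sample size does not depend on this point.

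**2. Does any reading make the data paired?** A before-and-after comparison within a person would be paired, but the sentence concerns baseline values only and its purpose is a comparison between groups. Matched pairs would be paired, but allocation is to two parallel arms with no matching. The partner test is the independent-samples one. No paired reading is left.

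**3. What happens if the text is followed with 15 per arm.** The signed rank statistic ranks the differences x(i) − y(i), so it changes when the control rows are reordered. The rank-sum statistic ranks all 30 values together and does not. One simulated skewed data set (15 per arm, log-scale SD 0.8, log-means 0 and 0.5), with one arm's rows shuffled 5,000 times, gave:

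| Test | p-value on the same 30 values |
|---|---|
| Rank-sum | 0.147 (one value) |
| Signed rank | 0.003 to 0.330, median 0.073; 30% of pairings below 0.05 |

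The range belongs to this data set. The dependence on row order is a property of the test.

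**4. Unequal arms.** With 16 and 14, for example, there are at most 14 pairs, so two participants must be dropped before the test can be computed.

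**5. Error rate.** In 5,000 simulated trials with no difference between arms and an arbitrary pairing fixed in advance, rejection at 0.05 was 4.2% for signed rank and 4.2% for rank-sum. So the defect is arbitrariness, not an inflated false-positive rate, provided that nobody chooses the pairing after seeing the data.

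**6. What a baseline p-value tells the reader at this size.** For the t-test with 15 per arm, the standard error of the difference in SD units is √(2/15) = 0.365.
- An observed imbalance of 0.5 SD gives t = 0.5/0.365 = 1.37 on 28 degrees of freedom, p = 0.18.
- The smallest imbalance that reaches p < 0.05 is 2.048 × 0.365 = 0.75 SD.

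An imbalance of half a standard deviation would therefore be reported as not significant, although it could matter for a prognostic variable.

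**The case against.** The strongest reply is that this is a slip of the pen. The test beside it is the independent t-test, so rank-sum was probably meant. An analyst with arm as a grouping variable would have to construct a pairing to run the wrong test, and would probably notice. That is plausible and lowers the likely harm. It does not remove the error: nothing else in the article corrects the name, and condensing a protocol does not turn one test into another. The point about baseline testing stands even if the name is a slip.

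It is also fair to say that little hangs on the comparison. The article attaches no action to its result: no covariate choice, progression decision or outcome model depends on it. That stands in full.

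A reader might infer stronger conclusions that the documents do not support:
- That baseline testing is invalid. Each test keeps about its nominal level (step 5); the tests are uninformative, not invalid.
- That the plan breaks its commitment to CONSORT. The article cites that statement but does not say what it asks of a baseline table, so the point cannot be settled from the documents.
- That a spurious baseline difference is close to an even bet. About 11 listed outcomes would give 1 − 0.95^11 = 43%, but only if they were independent. Several of the scales overlap (PHQ-9, GAD-7, MacNew, EQ-5D-5L), and the figure counts t-tests too, so it says nothing about the signed rank error.
- That removing the baseline tests settles the conflict with "No formal hypothesis testing will be performed". That conflict runs through the whole section, which also plans post hoc tests on significant differences.

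**Conclusion.** The concern holds in a limited form. The signed rank test is the wrong test for two independent randomised arms. Taken literally, it gives an answer that depends on an arbitrary pairing, and it cannot use all participants if the arms are unequal. Whichever test is used, a baseline p-value after randomisation does not show whether an imbalance matters, and it fits poorly with the section's own statement on hypothesis testing.

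The consequence is confined to the baseline table, so this ranks as a minor to should-fix correction. The conclusion about the test rests only on the article's text and the definition of the test. The simulated p-values are illustrations under assumed log-normal data and do not predict this trial's results.

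**What to change.** Preferred: delete the sentence on baseline comparisons and let the planned descriptive summaries by arm stand alone. Readers can then judge any imbalance by its size and clinical relevance.

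If a non-parametric comparison between arms is kept there or elsewhere, replace 'Wilcoxon signed rank' with 'Wilcoxon rank-sum (Mann-Whitney)'.

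Either change costs one sentence and alters no data collection, sample size or outcome. Adjusting the outcome analyses for the baseline value would be a sensible way to handle chance imbalance, but that is a separate decision about the outcome model and is not needed to correct this error.
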